**Fig. 2 Fig2:**
[figure not shown]
Logic model describing the multi-level, multi-component TRUE HAVEN intervention and measurable outcomes

In addition, a subset of participants in each neighborhood will be asked if they are willing to participate in a focus group to explore implementation outcomes (e.g., satisfaction with the intervention and content delivery, perceived usefulness of the intervention) in the second half of or right after their 6-month enrollment period. These focus groups will include a purposive sample of 20 participants each half year, stratified by gender, race, and age, and each focus group will have no more than 8 participants. We will hold separate focus groups with men and women to understand if and how various factors affect men and women differently. The focus group will be no longer than 90 min in length and participation will be voluntary – the participants will still be able to complete the other parts of the program if they elect not to join the focus group. We will also collect data on implementation outcomes (i.e., adoption, acceptability, feasibility, appropriateness) from the staff members delivering the financial education (i.e., housing counselors; other ULSC staff). This will be in the form of bi-annual assessments programmed in Qualtrics and administered by the program manager of this study in person or over the phone. We will also recruit a sample of staff for focus groups yearly to qualitatively explore these outcomes. Participant dropout and retention will be monitored.

The above procedures all refer to the housing assistance part of the intervention. In addition, we will also recruit 50 community members from each neighborhood to be trained in trauma-informed counseling by our partners at Clifford Beers Clinic. We will ask them to track and report the number of people they counsel each week to the program manager. Some of them may be asked to participate in implementer focus groups as well. Outcomes will be assessed in aggregate at the neighborhood level, including how many people were newly referred for mental health care and neighborhood rates of depression, anxiety, and symptoms of post-traumatic stress. Still, we will not be obtaining data directly from the individuals who are counseled or seek mental health care.

We train personnel at ULSC in informed consent procedures and confidentiality. All surveys will be administered by an intake specialist at ULSC, who has completed training that includes: (a) basic interviewing techniques, (b) human subject rights, (c) issues of confidentiality and anonymity, and (d) details of the survey instrument. Interviewer training will be a detailed process to ensure that the purposes and sponsorship of the research are explained thoroughly, that questions are phrased in a non-threatening manner, that the procedures for confidentiality are clearly understood, and that interviewers are skilled in communicating these facts to potential respondents. Prior to working on the project, the interviewer will sign an agreement of confidentiality prohibiting any inappropriate use of information as outlined in this proposal, institutional review board (IRB) standards, or the Certificate of Confidentiality.

### Neighborhood-level randomization

Neighborhood-level randomization was carried out by the TRUE HAVEN CAB on August 5th, 2022 by randomly drawing names without replacement of the six participating neighborhoods from a box. While overseeing and monitoring the implementation of TRUE HAVEN, CAB members are also part of the intervention as implementers and/or as part of the larger SC responsible for changing discriminatory policies and lowering barriers to achieving housing stability and accessing mental health. They will also be the decision-makers on program adaptations. The schematic diagram for the randomization is in Fig. 3, following the Consolidated Standards of Reporting Trials (CONSORT) extension for the stepped wedge cluster randomized trials [29] (see Supplemental File 2 for completed CONSORT checklist) and Standard Protocol Items: Recommendations for Interventional Trials (SPIRIT) [30] (see Supplemental File 3 for the completed SPIRIT checklist). The SPIRIT diagram is presented in Fig. 4.

**Fig. 3 Fig3:**
[figure not shown]
Flow diagram for the recruitment and assessment of participants in the housing assistance component of TRUE HAVEN.

**Fig. 4 Fig4:**
[figure not shown]
Schematic diagram for the community-level randomization (T: treatment period; C: control period)

### Outcome measures and data collection

#### Primary outcome

The primary outcome of this study is the neighborhood incident gun violence rate. These administrative data will be provided monthly by the New Haven Police Department. This outcome is assessed at the neighborhood level.

#### Secondary outcomes

The first secondary outcome is neighborhood social cohesion, which is measured by the Social Cohesion sub-scale of the Sampson Collective Efficacy Scale [31]. It is a neighborhood-level outcome on residents’ perception of the strengths of relationships and solidarity among their neighbors. Social cohesion and additional neighborhood-level rates of depression, anxiety, and symptoms of post-traumatic stress will be provided by DataHaven yearly from a representative sample. The other secondary outcomes are measured among participants in the housing stability component, and include (1) participant self-efficacy: participant belief in their capacity to execute behaviors necessary to achieve goals, measured by the Generalized Self-Efficacy Scale [32]; (2) perceived health and well-being, to be assessed by the 100 Million Healthier Lives Adult Well-being Assessment [33] including measures on subjective well-being, general health, health problems, sense of direction and purpose in life, emotional support, and sense of belonging to community; (3) financial security, assessed by financial readiness for an emergency. These participant-level secondary outcomes will be measured every six months.

#### Implementation outcomes

Following the RE-AIM implementation science framework [25], assessments on implementation outcomes are collected by research coordinators at baseline and every six months following the initiation of the intervention in each neighborhood. We will use validated scales to assess implementation outcomes, including measures of acceptability, appropriateness, and feasibility by Weiner, et al [18], and measures of fidelity and reporting adaptations and modifications following the Framework for Reporting Adaptations and Modifications-Enhanced (FRAME) [34].

#### Data collection

For the primary outcome, the New Haven Police Department will provide neighborhood-level data on gun assaults. DataHaven, a not-for-profit organization that collects neighborhood-level data on community wellbeing and social cohesion, is our key community partner who will provide neighborhood-level outcomes each year of our study. Connecticut Housing Finance Authority (CHFA) will provide neighborhood-level data on home ownership, loan denial, eviction and foreclosure. In addition, for participants recruited to the housing assistance program, information on sociodemographic backgrounds will be collected at the baseline, and questionnaires will be administered verbally either by phone or in-person at the 6-month visit by a housing counselor, and at the 1-year and 2-year time points by phone by the program manager. For qualitative and implementation outcomes, there may be additional *de novo* questions added that stakeholders think are important to include. Likewise, focus group questions will be developed in collaboration with our CAB and implementation partners and submitted to the IRB for approval prior to holding any focus groups.

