### Objectives and hypotheses

Among communities with well-being damaged by gun violence, our study aims to compare effectiveness of TRUE HAVEN vs. conditions as usual on the incidence of gun violence at the neighborhood level. We hypothesize TRUE HAVEN will be associated with lower incident gun violence compared with conditions as usual. Second, we will compare the effect of TRUE HAVEN vs. conditions as usual on secondary outcomes including social cohesion of the neighborhood, and among participants enrolled in the housing stability component, changes in their self-efficacy, perceived health and well-being, and financial security. We hypothesize that the intervention will lead to improvement in these outcomes. Lastly, for each intervention component, we hypothesize the following: (1) pairing rigorous financial education with financial support for home ownership and rental assistance will increase families’ housing stability and neighborhood cohesion, changing the neighborhood context and decreasing gun violence; (2) training trusted community members in trauma-informed counseling will provide needed psychosocial support for families and communities affected by gun violence, heighten awareness of community members affected by trauma, destigmatize accessing mental healthcare, and improve access to mental healthcare, thereby breaking the cycle of trauma and violence; and (3) convening a coalition of decision-makers and influencers at the city and state level to address structural and policy barriers that prohibit achieving housing stability and accessing mental healthcare, thereby actively dismantling structurally racist policies and facilitate components (1) and (2).

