#### Recruitment, procedures, and follow-up

For the housing stability component, the recruitment and assessment processes are described above and summarized in Fig. 2. The hypothesized determinants were originally developed based on the Consolidated Framework for Implementation Research (CFIR) and grouped by levels [28]. Participants meeting the inclusion criteria and who consent to participate will complete a baseline assessment on the day of enrollment. Participants will then engage in a comprehensive, tailored financial education and counseling program through the ULSC to address their housing instability. The education component includes learning objectives such as understanding how credit scores work, creating and maintaining a budget, developing habits to save money, setting sound financial goals, and avoiding debt. The financial education program is milestone-based, so participants move forward to the next lesson only after prior content has been mastered. This approach fosters self-efficacy and confidence and ensures graduates of the program are equipped with the skills needed to maintain financial security after financial supports expire. Financial supports in the form of rental assistance or down payment assistance and/or low-interest home loans will be provided to participants when the appropriate milestones have been achieved. Most people are able to complete the financial education program within six months. At the beginning and end of their course, participants will complete a knowledge assessment to assess their understanding of financial topics (e.g., how credit reports work and how much money should be in savings) and their perceptions of the acceptability, appropriateness, and feasibility of the program. At the time of enrollment and at 6-months, 1-year and 2-years, ULSC will contact participants by phone to assess their housing situation (i.e., they remained in their home/apartment, moved to a different home/apartment and if so why, were evicted, underwent foreclosure) and financial situation (i.e., how much in savings). We will also assess other outcomes such as self-efficacy, perceived health and well-being, and financial knowledge.

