### Limitations

First, the neighborhoods under intervention are geographically close to each other and social networks spanning across neighborhood are expected. Benefits received from the intervention among those in one neighborhood may affect those in another, which leads to the spillover of the treatment effect. Second, TRUE HAVEN is a non-blinded study due to practical considerations, and the sequenced time of initiation of the intervention across the neighborhoods are known. Although the primary outcome of gun violence incident rate is perhaps less at risk of bias from lack of blinding, certain secondary outcomes could result in bias due to non-blinding. Third, our study site is located in New Haven, CT, a northeast U.S. city, and has potentially limited generalizability to other locations where the causes of gun violence and the amount of community resources may be different. Fourth, there may be exogenous factors that affect rates of gun violence over the course of 5 years (e.g., changes in funding, elections of new political leaders) that make the results more difficult to interpret. We can use data from neighborhoods in similar Connecticut cities, Bridgeport and Hartford, that can serve as additional comparisons to identify secular trends.

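### The article gives two incompatible rules on who administers the participant surveys, and one of them has program-delivery staff collect the 6-month self-reports

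*Protocol article*

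**What the plan says.** Two places in the protocol article assign the participant surveys.

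- **Recruitment, procedures, and follow-up:** "All surveys will be administered by an intake specialist at ULSC, who has completed training that includes" interviewing technique, confidentiality and the instrument itself. The rule has no exception for follow-up.
- **Data collection:** the questionnaires are verbal, by phone or in person at 6 months, and are given "at the 6-month visit by a housing counselor, and at the 1-year and 2-year time points by phone by the program manager".

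Three further statements bear on the point.

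- The Recruitment subsection describes "the staff members delivering the financial education (i.e., housing counselors; other ULSC staff" when it explains who supplies the staff-level implementation data. Housing counselors are therefore delivery staff.
- The same subsection says participants "will complete a baseline assessment on the day of enrollment" but does not say who gives that assessment.
- Objectives and hypotheses sets as secondary targets "changes in their self-efficacy, perceived health and well-being, and financial security". Under Secondary outcomes, self-efficacy and well-being are questionnaire scales, and financial security is judged by readiness for a financial emergency.

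The Limitations subsection concedes that "certain secondary outcomes could result in bias due to non-blinding". It does not mention who asks the questions.

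**The concern.** The outcomes at issue are answers spoken aloud to another person, so they can depend on who is asking. At 6 months, under the Data collection text, that person holds a role that delivers the program being evaluated. If a different role took the baseline answers, a change in score reflects both the passage through the program and the change of interviewer.

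At stake is the interpretation of the participant-level secondary outcomes. Lack of blinding cannot be avoided in this trial, but the use of delivery staff as outcome interviewers can. The general caveat on non-blinding neither covers that choice nor resolves the conflict between the two rules.

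**Working it through.** The article states no figure for an interviewer effect, so there is nothing of that kind to reproduce. The check is a comparison of texts, then an identifiability check, then an illustration on assumed values.

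**1. Who asks, under each reading**

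| Visit | General rule (Recruitment) | Data collection text |
|---|---|---|
| Baseline | Intake specialist | Not named |
| 6 months | Intake specialist | Housing counselor, phone or in person |
| 1 year | Intake specialist | Program manager, phone |
| 2 years | Intake specialist | Program manager, phone |

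The columns disagree at all three follow-up visits. Table 2 does not settle it. It lists the project manager and implementers as assessors of self-efficacy and perceived well-being, and implementers are defined under Overall design as the ULSC staff responsible for the housing component. That could include either role.

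**2. Can visit and interviewer role be separated?**

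Take the combined reading: general rule at baseline, Data collection text afterwards. A model with an intercept, three visit indicators (6 months, 1 year, 2 years) and two role indicators (counselor, manager) has 6 columns. Within it:

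- counselor indicator = 6-month indicator;
- manager indicator = 1-year indicator + 2-year indicator.

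The rank is therefore 6 − 2 = 4. For baseline versus 6 months alone there are 3 columns and rank 2. Role is fully aliased with visit, and covariate adjustment cannot separate them. The staggered start does not help, because visits are timed from enrollment and the sequence of roles is the same in every neighborhood. Only the change from 1 to 2 years keeps one role and one mode.

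Under the general rule alone, one role asks throughout and there is no aliasing.

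**3. Illustration only**

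Assume zero true change, an interviewer shift of d standard deviations, a standard deviation of change equal to 1 SD, no clustering and no dropout. A two-sided 5% paired z-test then rejects with probability

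Φ(d√n − 1.96) + Φ(−d√n − 1.96).

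The sample sizes come from Justification of sample size: about 1,400 participants in total, and 1,400 / 6 ≈ 233 per neighborhood.

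| d (assumed) | n = 233 | n = 1,400 |
|---|---|---|
| 0 | 0.050 | 0.050 |
| 0.05 | 0.119 | 0.465 |
| 0.10 | 0.333 | 0.963 |
| 0.20 | 0.863 | about 1.000 |

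For example, with d = 0.10 and n = 233, d√n = 0.10 × 15.26 = 1.526, which gives 0.333. The protocol plans generalized estimating equations, not this test, and no value of d comes from the documents. The table shows only that a modest shift could matter at these sample sizes.

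**The case against.** The strongest reply is that the aliasing is conditional. The general rule says all surveys, and if it governs, one trained role asks at every visit. This stands: the aliasing follows only from the combined reading, and the intake specialist at baseline is itself inferred from the general rule. The contradiction remains whichever rule was intended.

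Other limits also stand. A reader might infer any of the following, and the documents support none of them:

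- **The interviewer changes at every visit.** The 1-year and 2-year surveys share a role. They are also not given by a counselor, so they offer a partial check on whether a 6-month gain persists.
- **Participants are interviewed by their own counselor.** The text says only that a housing counselor does it.
- **The counselor collects ratings of the program's acceptability.** Implementation outcomes assigns such measures to research coordinators, and Table 2 lists the project manager and investigators for participants' ratings. The Recruitment subsection places participants' ratings at the start and end of the course without naming who collects them. That assignment is unclear, but it is not given to the counselor.
- **The bias favours the program, or can be set against the 10 to 12 point detectable differences.** No passage gives a direction. Those differences are for binary outcomes such as homeownership and improved credit score, not for these scales.

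Nor is the intake specialist's neutrality shown. The role sits within ULSC, and other ULSC staff are counted among those delivering the education. The fix has to allow for this.

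**Conclusion.** The contradiction is certain, because the two rules differ at all three follow-up visits. The consequence is conditional. If the Data collection text is followed after a baseline taken by the intake specialist, interviewer role is aliased with visit for every baseline-to-follow-up change in the verbally collected self-reports, and the 6-month answers are given to delivery staff. This is a potential confounding built into data collection, not a demonstrated bias, and its size and direction are unknown.

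Its reach is limited to self-reported outcomes in the housing component. Gun violence rates from the police and the neighborhood data from DataHaven and CHFA are unaffected. It is worth correcting because the source of bias is avoidable and the correction is inexpensive. It does not threaten the primary analysis.

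**What to change.** Reconcile the Recruitment and Data collection subsections so that one trained, existing role with no part in delivering the program gives the self-report questionnaires at baseline, 6 months, 1 year and 2 years, in the same mode as far as possible. This could be the intake specialist, provided that person does not deliver the education, or another existing study role such as the program manager or the research coordinators. Name the baseline administrator explicitly. State in one place who collects participants' acceptability ratings, in line with Recruitment, Implementation outcomes and Table 2.

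Enrollment opened on February 1, 2023, so some surveys may already have been taken under mixed roles. For those, record interviewer role and mode for each survey and report the limitation.

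The cost is workload and scheduling. If one role takes over all follow-up, that is at most 1,400 × 3 = 4,200 interviews, before dropout. If the program manager, who already holds the 1-year and 2-year surveys, also takes the other two visits, at most 1,400 × 2 = 2,800 interviews move. This is a shift between existing roles, but the documents do not show whether those roles have the capacity.

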#### Implementation-focused process evaluation

Our implementation-focused process evaluation of TRUE HAVEN, grounded in the RE-AIM [3] and Proctor [35] frameworks, will include minutes from CAB and steering committee meetings, minutes and logs from study team meetings, site visits, as well as interview data collected from enrolled participants. The logic model describing the multi-level, multi-component TRUE HAVEN intervention and measurable outcomes are presented in Fig. 5. Protocol modifications, if needed, will be guided by FRAME [34]. We will assess the following domains: (1) fidelity to intervention and strategies; (2) cost of interventions and strategies; (3) number and percentage of individuals that complete program; (4) number of services coordinated by each coordinator; (5) number of services coordinated for each family; and (6) new policies/practices that reduce barriers for families.

**Fig. 5 Fig5:**
[figure not shown]
Standard Protocol Items: Recommendations for Interventional Trials (SPIRIT) flow diagram for TRUE HAVEN.

### Statistical considerations

#### Justification of sample size

The primary aim of this study is to compare the intervention effect of TRUE HAVEN versus control on average yearly shooting victim rates. With an average of 10,295 residents per neighborhood per year, leading to approximately 432,390 person-steps of follow-up over 3.5 years, for a two-sided test between Poisson rates with a Type I error of 0.05, intra-cluster correlation coefficient (ICC) of 0.50 as currently estimated in these 6 neighborhoods of New Haven, and a baseline shooting rate of 6 shooting victims per 10,000 persons per step in the control period as currently observed on average in these New Haven neighborhoods, our study will have about 80% power to detect a 28% decrease or greater in the primary outcome, average neighborhood shooting rates, in relation to the full TRUE HAVEN intervention package [24, 36].

For individual-level outcomes of the housing assistance component, with approximately 1400 total participants (i.e., 233 participant individuals/families per neighborhood group) enrolled during the 3.5 year study period, that is, about 33 participants per neighborhood per 0.5 year step, for binary outcomes (e.g., % homeownership, % housing costs < 30% of income, % improved credit score), for a two-sided test of the difference between proportions with a Type 1 error of 0.05, with ICCs as low as 0.01 and as high as 0.2, our study will achieve at least 80% power to detect an increase with the TRUE HAVEN intervention of at least 2.4% points for outcomes where the baseline proportion is 1% or less, 10% points for outcomes where the baseline proportion is 20% or less, and 12% points for outcomes where the baseline proportion is 40% or less.

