**Design:**

TRUE HAVEN is an ongoing, multi-level intervention with three primary components: financial education paired with housing support (individual level), trauma-informed counseling (neighborhood level), and policy changes to address structural racism (city/state level). Six neighborhoods with among the highest rates of gun violence in New Haven, Connecticut, will receive the individual and neighborhood level intervention components sequentially beginning at staggered 6-month steps. Residents of these neighborhoods will be eligible to participate in the housing stability and financial education component if they were recently incarcerated or are family members of currently incarcerated people; participants will receive intense financial education and follow-up for six months and be eligible for special down payment and rental assistance programs. In addition, trusted community members and organization leaders within each target neighborhood will participate in trauma-informed care training sessions to then be able to recognize when their peers are suffering from trauma symptoms, to support these affected peers, and to destigmatize accessing professional mental health services and connect them to these services when needed. Finally, a multi-stakeholder coalition will be convened to address policies that act as barriers to housing stability or accessing mental healthcare. Interventions will be delivered through existing partnerships with community-based organizations and networks. The primary outcome is neighborhood rate of incident gun violence. To inform future implementation and optimize the intervention package as the study progresses, we will use the Learn As You Go approach to optimize and assess the effectiveness of the intervention package on the primary study outcome.

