### Study context and institutional review

New Haven, CT, is a small city that, like most cities in the US, experiences significant neighborhood-level health inequities. There is an approximate 12-year gap in life expectancy between the low-income, Black/Latinx neighborhoods that had been redlined as Grade D neighborhoods decades ago, where banks systematically denied loans for homes and businesses, compared with those that were rated Grade A (see Supplemental Fig. 1) [26]. These neighborhoods also experience higher rates of gun violence, incarceration, unemployment, and housing instability [1]. Mean rates of gun violence between 2011 and 2020 in our six predominantly Black/Latinx neighborhoods range from 70 to 248 shootings per 100,000 population, compared with 15–38 shootings per 100,000 population in non-redlined neighborhoods and 4.4 shootings per 100,000 population nationally. Our team has recognized that large-scale, community-wide, systemic interventions are needed to curb the incidence and effects of gun violence.

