#### Statistical analyses

For the primary outcome, we will use a log-Poisson mixed effects model for the neighborhood shooting rates $$\text{log}\left[\text{E}\left({Y}_{ij}=1|{\varvec{X}}_{ij}\right)\right]= {\beta }_{0} + {\beta }_{1}{X}_{ij}+{\varvec{\beta }}_{2}^{{\prime }{\varvec{t}}_{ij}}+{N}_{i}+ {b}_{i}$$, where $${Y}_{ij} \text{i}\text{s}$$ the number of individuals affected by gun violence for the *ith* neighborhood, *i = 1,…6*, at the *jth* step, *j = 1,…,7*,$${X}_{ij}$$is the intervention status for the $$i$$^*th*^ neighborhood at the $$j$$^*th*^ step, $${\varvec{t}}_{ij}$$ is an indicator function for the step number, $${N}_{i}$$ is the offset corresponding to the population of the $$i$$^*th*^ neighborhood, and $${b}_{i}$$ is a mean-zero random neighborhood effect. $$\text{e}\text{x}\text{p}\left[{\beta }_{1}\right]$$ is the parameter of interest, the rate ratio for the overall intervention effect and the natural exponent of the elements of $${\varvec{\beta }}_{2}$$ are the rate ratios for the 6 step time effects. A generalized estimating equations approach [37] will be taken for estimation and inference will use the robust score test, and an independence working correlation matrix to account for correlations within neighborhoods in inference. Many secondary analyses of the primary endpoint can be conducted. With 6 neighborhoods, residual confounding is possible, and in secondary analysis, the model will include adjustment for potential neighborhood-level confounders, such as median income, percent unemployed, and population density. Secondary analysis of the primary outcome will consider modification of the intervention effect by pre-specified potential modifiers, such as race/ethnicity composition of the neighborhood, median neighborhood income and season. These interactions will be assessed by robust score tests of the suitable cross-product terms.

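### The stated 80% power for a 28% reduction in shootings does not follow from the plan's own inputs under its step-adjusted primary model, which gives roughly 28% to 44%

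*Protocol article*

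**What the plan says.** Under Justification of sample size, the protocol article bases the primary comparison on these inputs:

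- exposure: "With an average of 10,295 residents per neighborhood per year, leading to approximately 432,390 person-steps of follow-up over 3.5 years";
- test: "for a two-sided test between Poisson rates with a Type I error of 0.05";
- clustering: "intra-cluster correlation coefficient (ICC) of 0.50 as currently estimated in these 6 neighborhoods of New Haven";
- control rate: "a baseline shooting rate of 6 shooting victims per 10,000 persons per step in the control period".

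From these it concludes that "our study will have about 80% power to detect a 28% decrease or greater in the primary outcome". The paragraph does not mention adjustment for step, and it does not say on what scale the ICC is measured.

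Under Statistical analyses, the primary model is a log-Poisson model over six neighborhoods and seven steps, with a population offset, an intervention term, a random neighborhood effect, and coefficients whose exponents "are the rate ratios for the 6 step time effects". Estimation is by GEE with an independence working correlation, and inference is by a robust score test.

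On roll-out, the abstract says that the six neighborhoods "will receive the individual and neighborhood level intervention components sequentially beginning at staggered 6-month steps". Table 1 agrees, with two new neighborhoods a year.

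**The concern.** In a stepped wedge the intervention indicator rises with calendar time, so adjusting for step removes much of the information about the intervention effect. A power figure that ignores this can be far too high. The counts are also small, at about six victims per neighborhood per half-year, so Poisson noise alone limits what can be detected. Step adjustment cannot reasonably be dropped: the Rationale section describes a decline in gun violence, a plateau, and a rise from 2019 that became rapid in 2020, and the Limitations section warns of exogenous influences over the five years.

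This is the only power justification for the primary outcome. If a null result is read against 80% power, it will look like evidence that the package does not achieve a 28% reduction, when the planned analysis would miss such an effect more often than not.

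**Working it through.** **Inputs from the article.** 10,295 residents per neighborhood; 6 neighborhoods and 7 steps; control rate 0.0006 per person-step; rate ratio 0.72, so |log RR| = 0.3285; two-sided 5%.

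**Assumptions.** Equal neighborhood sizes, one neighborhood crossing per step, intervention status staying on after crossover, and no overdispersion at the neighborhood-step level. The roll-out pattern is taken from the text.

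**Basic quantities.**
- Exposure: 6 × 7 × 10,295 = 432,390 person-steps, matching the article.
- Expected victims per cell under control: 10,295 × 0.0006 = 6.18; over 42 cells, 259.
- Control cells: 1 + 2 + 3 + 4 + 5 + 6 = 21, leaving 21 intervention cells.
- Power = Φ(|effect| / SE − 1.96).

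**1. Reproducing the stated 80%.** Two things are needed: leave out the step effects, and multiply the Poisson variance by (1 − 0.50).
- Rate difference: 0.28 × 0.0006 = 0.000168.
- Variance per cell: 0.5 × 0.0006 / 10,295 = 2.914 × 10⁻⁸.
- Sum of squares of the intervention indicator within neighborhoods: (6 + 10 + 12 + 12 + 10 + 6) / 7 = 8.0.
- SE = √(2.914 × 10⁻⁸ / 8.0) = 6.035 × 10⁻⁵; z = 2.784; power 79.5%.

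That takes the ICC at person level. Taking it at neighborhood-step level, again as a share of a fixed total variance, gives 81.0%.

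**2. Plain two-sided Poisson comparison, no clustering, no step effects.**
- Expected victims: 21 × 6.18 = 129.7 under control and 129.7 × 0.72 = 93.4 under intervention.
- SE(log RR) = √(1/129.7 + 1/93.4) = 0.1357; z = 2.42; power about 68%.
- 80% power needs a reduction of about 32%.

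Using the null variance raises power to 73.5%, still short of 80%.

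**3. Six step effects added, full Poisson variance.** With τ² the between-neighborhood variance on the log scale, each neighborhood's seven log rates have covariance diag(1/μ) + τ²J, where μ is the expected count and J the all-ones matrix. The SE comes from the inverse of the summed information matrix.

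| τ² | SE(log RR) | Power at RR 0.72 | Reduction for 80% power |
|---|---|---|---|
| 0 | 0.182 | 44% | 42% |
| 0.04 (CV about 0.2) | 0.210 | 35% | 47% |
| 0.162 (= 1/6.18: between-neighborhood variance equals Poisson variance of a cell) | 0.228 | 30% | 50% |
| very large (neighborhoods effectively fixed) | 0.239 | 28% | about 52% |

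**4. Step effects added to the convention in step 1.** The residual sum of squares falls from 8.0 to 3.33, so SE = √(2.914 × 10⁻⁸ / 3.33) = 9.35 × 10⁻⁵, z = 1.80 and power is 43.5%. The neighborhood-step version gives 46.8%. Averaging the variance over arms gives at most about 53%, and using the intervention-arm rate in every cell at most 60%.

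**5. The planned test.** Simulating the independence-GEE robust score test with step effects (20,000 trials per setting, RR 0.72):

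| Between-neighborhood CV | Simulated power |
|---|---|
| 0 | 23% |
| 0.2 | 16% |
| 0.4 | 9% |
| 0.5 | 7% |

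With six clusters the robust score test is conservative: its simulated type I error was 3.9% at CV 0 and 2.9% at CV 0.4.

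**The case against.** The strongest reply is that the article does not say on what scale the ICC of 0.50 is measured, and the calculation rests on cited methods that are not reproduced. The inputs therefore do not pin down a single correct power, and no reader can be sure how 80% was obtained. That stands, and it limits what can be said in three ways.

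- A reader might take 28% power and a 52% detectable reduction as the answer. They are the limit in which neighborhoods are effectively fixed. With the random intercept that the article writes down, power could be as high as 44%. Nor is either figure the power of the GEE score test that is planned.
- A reader might infer that the planned test has almost no power, under 5%. In simulation that appears only at a between-neighborhood CV of 0.8 to 1.0, and the article states no such value.
- A reader might infer that the sponsor misapplied a person-level ICC. The documents do not show this. The neighborhood-step convention gives 81.0%, and a one-sided 5% test without clustering or step effects gives 78% to 82%, although the article says two-sided.

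The reply does not rescue the figure. No two-sided, step-adjusted reading that was tried exceeded 60%. The two-sided routes to about 80% omit the step effects and shrink the Poisson variance. Both conflict with the stated model: it contains step effects, and under a log-Poisson model the variance given the neighborhood effect equals the mean.

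**Conclusion.** The point holds. The stated 80% power for a 28% reduction is not delivered by the article's inputs under its own primary model. With full Poisson variance and step effects, power is about 28% to 44%, and 80% power needs a reduction of about 42% to 52%. The simplest two-sided Poisson comparison reaches only about 68%.

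The upper end of the range requires no between-neighborhood variation. The article reports ten-year mean rates that "range from 70 to 248 shootings per 100,000 population" across the six neighborhoods, a ratio of 248/70 = 3.5, so that end is unlikely to apply. The planned GEE score test has lower power still.

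These results rest on the assumptions listed with the calculation. Extra step-level overdispersion would lower power further. How the sponsor obtained 80% is not known, and the conclusion does not depend on it.

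**What to change.** In Justification of sample size:

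1. State the scale on which the ICC of 0.50 was estimated (person, neighborhood-step rate, or share of total variance), and the between-neighborhood variance that it implies.
2. Recompute power for the analysis actually planned: step-adjusted, six neighborhoods, independence GEE with the robust score test. With so few clusters, simulation is the safer route.
3. Restate either the power for a 28% reduction or the reduction detectable with 80% power, with the roll-out and variance assumptions beside it.

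The replacement figures should come from the sponsor's own variance estimate. The range given here shows the size of the gap and is not text to insert. The cost is a rewritten paragraph, a short simulation and a less favourable stated figure. No extra enrolment and no change to trial conduct are needed.
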